#### Primary objective

The primary objective of AIMI-HF is to compare the effect of HF imaging strategies on the composite clinical endpoint of cardiac death, MI, resuscitated cardiac arrest and cardiac re-hospitalization (WHF, ACS, and arrhythmia). Patients with HF due to an ischemic heart disease (IHD) etiology of LV dysfunction will follow HF imaging strategy algorithms according to the question(s) asked by the physicians (Is there ischemia and/or viability?), in agreement with their local practices for standard and alternative imaging.

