### Blinding

The study is not blinded given the nature and purpose of the interventions. Knowledge of imaging results and potential gained from the intervention will need to be considered to implement the appropriate treatment strategy. Therefore, performance bias (that is, systematic differences between groups in the care provided or exposure to factors other than the interventions of interest) and attrition bias (that is, systematic differences between groups in withdrawals from the study) may occur. Detection bias is still a potential concern, but an independent assessor will evaluate the objectively defined primary outcome and an adjudication committee will independently review and adjudicate each clinical event blinded to treatment randomization.

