### Subject evaluation

At baseline, demographic and clinical data will be collected from all participants on standardized case report forms. These data will be collected from the most recent, routine history and physical examination that has been completed by the treating physician. Quality of life questionnaires (EuroQol and Minnesota Living with Heart Failure) will be administered. In addition, the above-mentioned laboratory samples will be collected. To address a secondary objective, whenever possible, an echocardiogram will be performed if LV ejection fraction has not been determined by echocardiography within 6 months prior to randomization. As much as possible, imaging procedures will be performed within 4 weeks after entry into the trial. Subsequent telephone follow-up and repeat blood work will be performed on a predetermined schedule (Table 2). If the patient cannot be reached by telephone for their final assessment, a query will be made at government or national health care resources to verify if any corresponding events have occurred since the last visit (search of corresponding codes for cardiac death, MI, cardiac arrest and cardiac re-hospitalization for WHF, ACS, or arrhythmia). A follow-up echocardiogram will be requested at one year (LV remodeling, LVEF). Within 3 months of the baseline scan the treating physician will be asked to record the HF management plan.

**Table 2 T2:** Patient assessment schedule

	**Baseline**	**3 months**	**6 months**	**12 months**	**18 months**	**24 months**	**36 months**	**48 months**
Imaging (SPECT, PET or CMR)	x							
Blood work	x			x				
Demographic and history	x							
Clinical data collected	x			x				
EuroQol questionnaire	x	x	x	x	x	x	x	x
MLWHF questionnaire	x	x	x	x	x	x	x	x
Telephone follow-up		x	x	x	x	x	x	x

*CMR* cardiac magnetic resonance, *MLWHF* Minnesota Living with Heart Failure, *PET* positron emission tomography, *SPECT* single photon emission computed tomography.

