#### Primary analysis (advanced versus standard imaging)

For the primary analysis, the time-to-event of the composite clinical endpoint of cardiac death, MI, arrest and cardiac re-hospitalization (WHF, ACS, arrhythmia) will be compared between the advanced modality (PET or CMR) to an approach with standard care using SPECT imaging using survival analysis. Kaplan-Meier survival curves of the primary endpoint will be compared between the advanced and standard modalities with the log-rank test. Potential confounding variables of the relationship between the imaging technologies and the primary endpoint will be assessed. In particular, propensity scores based on patient factors (for example, in/outpatient, NYHA class, HF duration, diabetes, atrial fibrillation) and site factors (for example, time-to-imaging, time-to-therapy) will be used in the analysis if necessary to adjust for potential differences. A Cox proportional hazard models will be used to assess the occurrence of the endpoints between the imaging technologies (model will include a group indicator variable) adjusting for any pertinent baseline differences identified. The proportional hazards assumption underlying the Cox model will be assessed.

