#### Economic evaluation

For secondary objective 5, a cost-effectiveness analysis of advanced versus standard modality groups will be conducted. Analysis will take the form of a cost-utility analysis with cost effectiveness assessed in terms of the incremental cost per quality life year. Analysis will incorporate data on resource use and patients utility values for the period from initiation of treatment to study termination. Resource use will be assessed through review of patient charts and patient utility values will be derived using the EQ5D and MLHF. A decision model will be created to estimate long-term costs and quality adjusted life years (QALYs) for all comparators. Uncertainty within the analysis will be assessed through Monte Carlo and other simulation techniques.

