### Study management

The IMAGE-HF trial is managed by an Executive Committee consisting of clinicians specialized in diagnostic imaging and/or heart failure and experts in biostatistics, physics and radiochemistry, as well as a larger Steering Committee consisting of members of the Executive Committee and representatives of all the initial study centers. (Table 3) In addition there is an events adjudication committee, which will independently review and adjudicate each clinical event blinded to treatment randomization. Since all the imaging approaches are part of standard clinical practice, no interim analysis is planned, but there will be independent data safety monitoring board (DSMB), which will review the safety data on a periodic basis; the frequency of the meetings and the charter governing the DSMB will be finalized at the first meeting of the DSMB.

**Table 3 T3:** Imaging Modalities to Assist with Guiding Therapy and the Evaluation of Patients with Heart Failure (IMAGE-HP) participating

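### The fallback database query covers only cardiac event codes, so for unreachable patients a death coded otherwise is not retrieved, dated or adjudicated

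*Protocol article*

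**What the plan says.** Subject evaluation sets the fallback: "If the patient cannot be reached by telephone for their final assessment, a query will be made at government or national health care resources". Its purpose is "to verify if any corresponding events have occurred since the last visit", and its content follows in brackets: "search of corresponding codes for cardiac death, MI, cardiac arrest and cardiac re-hospitalization for WHF, ACS, or arrhythmia". These categories are the components of the primary composite as defined under Primary objective. No query of vital status or of death from any cause is listed.

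Blinding states that "an adjudication committee will independently review and adjudicate each clinical event blinded to treatment randomization", and Study management repeats it. The primary analysis is time to event: "Kaplan-Meier survival curves of the primary endpoint will be compared between the advanced and standard modalities with the log-rank test". Under Economic evaluation, "A decision model will be created to estimate long-term costs and quality adjusted life years (QALYs) for all comparators".

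The article does not say how a patient is handled when the query finds nothing. The Registry section applies the same evaluation rules to registry patients, so the fallback also serves the PET versus CMR comparison.

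**The concern.** Whether a death is cardiac is one of the main judgements that a blinded committee exists to make. Here the cause recorded in a routine database decides whether the committee sees the death at all. A cardiac death filed under an unspecified cause would be an endpoint event that is never reviewed. A non-cardiac death is not an endpoint event, but its date is needed to end the patient's time at risk and to stop the accrual of QALYs.

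Death is one reason why a patient cannot be reached, so the query is narrow in the group where vital status is most uncertain. The trial is open-label, and Blinding itself names attrition bias as possible. Any difference between arms in who stays reachable would then carry over into event capture.

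**Working it through.** **1. What each part needs, against what the query returns**

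| Use | Needs | Cardiac-code query returns |
|---|---|---|
| Adjudication of each clinical event | Every death, for a ruling on cause | Only deaths already coded cardiac |
| Kaplan-Meier and log-rank | Event date, or a valid end of time at risk | No date for other deaths |
| QALYs | Date of death from any cause | As above |

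**2. Why the no-hit date matters.** Two simple rules are possible without vital status.
- Censor at the query date: a patient who died of a non-retrieved cause stays at risk after death.
- Censor at last contact, but count hits found after last contact: unreached patients contribute later events without the matching event-free time, which raises their apparent hazard.

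Neither is clean. Consistent handling needs the date of death and the last date that the database covers.

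**3. The plan's own figure.** Inputs from Sample size: 1-year rates of 40% (standard) and 30% (advanced), 2:1 allocation, two-sided 0.05, 80% power, 2.5 years of uniform accrual, 1 year minimum follow-up, 10% loss. With exponential hazards:
- λS = −ln(0.60) = 0.511 and λA = −ln(0.70) = 0.357 per year; HR = 0.357/0.511 = 0.698.
- The Lachin-Foulkes formula gives 448.9; 448.9/0.9 = 499. With loss entered as a 10% yearly hazard it gives 496. The stated 495 is reproduced.
- Schoenfeld events: (1.96 + 0.842)² / [(1/3)(2/3)(ln 0.698)²] = 274.

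**4. Non-cardiac deaths all missed and kept at risk to study end (the extreme case).** The yearly non-cardiac death rate m is an assumption. Observed rate = expected events / (true person-time + false person-time after death), averaged over follow-up of 1 to 3.5 years. False person-time for follow-up u is ∫₀ᵘ m·exp(−(λ+m)s)·(u−s) ds.

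| m per year | Standard | Advanced | Ratio |
|---|---|---|---|
| 0 | 0.511 | 0.357 | 0.698 |
| 1% | 0.504 | 0.352 | 0.699 |
| 3% | 0.489 | 0.342 | 0.699 |
| 5% | 0.476 | 0.333 | 0.700 |

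Absolute rates fall in both arms and the ratio hardly moves.

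**5. Endpoint events missed equally in both arms.** Power = Φ(√(D × 2/9) × |ln 0.698| − 1.96), with D the events that remain of 274. If an assumed 1%, 2%, 5% or 10% are missed, power falls from 80.0% to 79.6%, 79.2%, 78.0% or 75.8%.

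**6. Endpoint events missed in one arm only.** To first order the ratio is scaled by the share of events captured. The shares are again assumed.
- 1% missed: 0.698 × 0.99 = 0.691 if in the advanced arm; 0.698/0.99 = 0.705 if in the standard arm.
- 5% missed: 0.698 × 0.95 = 0.663; 0.698/0.95 = 0.735.
- 10% missed: 0.698 × 0.90 = 0.628; 0.698/0.90 = 0.776.

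These are shares of all events in an arm. A missed death counts here only if the patient had no earlier composite event.

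**The case against.** The strongest case on the other side has five parts.

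- **The search mirrors the endpoint.** Non-cardiac death is not in the composite, so a reader who counts such deaths as missed primary events goes too far. This stands. They bear on censoring and QALYs.
- **False survivors.** A reader might infer that the dead are carried as event-free survivors. The article states no rule for a patient with no hit. If such patients are censored at last contact, no false survival time arises, and the rule may stand in a full protocol or analysis plan that is not shown. This stands, so step 4 is an extreme case and not a description of the plan.
- **Coding in place of adjudication.** A reader might infer that database coding replaces the committee. Nothing exempts retrieved events from blinded review, so the gap concerns only deaths that the query does not return. The operational code list is also not shown, so how far its cardiac categories reach into vague codes is unknown.
- **Other routes.** Table 2 schedules seven calls, adverse events are to be documented, and resource use comes from charts. Any of these may reveal a death. The article does not show that they do so for a patient who can no longer be reached.
- **Size.** It is tempting to take the 10% loss allowance, 0.10 × 495 = 49.5 patients, and multiply by a guessed share of deaths. That 10% is a sample-size allowance, not the share unreached at the final call, and no document gives the second factor. No patient count is supported.

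What remains is a stated query that leaves out death from any cause, beside a stated promise to adjudicate each clinical event.

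**Conclusion.** The point holds in a limited form. For patients not reached at the final assessment, the query as written does not return a death coded as non-cardiac or of unspecified cause. The committee therefore cannot classify it by this route, and the date needed for censoring and for QALYs is not obtained.

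The effect on the primary comparison is likely small. The ratio is at most 0.700 against 0.698 in the extreme case of step 4, and power is 78.0% if 5% of events were missed equally in both arms. Both rest on exponential hazards and assumed loss rates. A larger effect needs a difference in unreachability between arms. The article concedes that this is possible but gives no figure for it. The QALY gap does not depend on such a difference. The number of patients affected is unknown.

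**What to change.** In Subject evaluation:

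- Extend the planned query to vital status, meaning death from any cause with date and recorded cause, alongside the cardiac event and hospitalization codes already listed.
- Send every retrieved death to the existing blinded committee for a ruling on cause.
- For the primary analysis, censor at the date of death if the death is adjudicated non-cardiac, and at the last date covered by the database if nothing is found.
- Use the same dates of death in the economic evaluation.

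The query and the committee are already planned. The cost is a slightly wider query and a few more records to adjudicate. No stated sample size changes.

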### Safety and ethics

This study was approved by the University of Ottawa Heart Institute Human Research Ethics Board, protocol #2010620-01H. In addition, before study initiation at each site, this protocol, and the informed consent form, as well as any advertisement for subject recruitment, was submitted for review and approval by each local participating site’s ethics committee charged with this responsibility and will be so submitted for future sites. These ethic committees will submit written notification of the approval to the investigator. This study will be conducted according to the Declaration of Helsinki, Good Clinical Practice and the TriCouncil Policy.

### Registry

Eligible and consenting patients that could not be randomized but undergo standard or advanced imaging based on clinical decisions, will be included in a registry. Measurement, subject evaluation and safety and ethics as outlined in the previous sections will apply to these registry patients. The registry patients for advanced imaging will be considered in the sample size calculation and data analysis (see below); however, the small number of patients expected to be part of the SPECT registry will not be considered in the primary analysis.

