**Discussion:**

AIMI-HF will be the largest randomized trial evaluating the role of standard and advanced imaging modalities in the management of ischemic cardiomyopathy and heart failure. This trial will complement the results of the Surgical Treatment for Ischemic Heart Failure (STICH) viability substudy and the PET and Recovery Following Revascularization (PARR-2) trial. The results will provide policy makers with data to support (or not) further investment in and wider dissemination of alternative ‘advanced’ imaging technologies.

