### Sample size

For the sample size determination, the estimated occurrence over one year of the composite clinical endpoint of cardiac death, MI, resuscitated cardiac arrest and cardiac re-hospitalization (WHF, ACS, arrhythmia) for PET is 27% and for standard care is 40%, based on the Ottawa-FIVE substudy [28] of the PARR-2 [27] study in which the composite event rates were 19% and 41%, respectively. These estimates were considered reasonable as it reflects the outcome rates that may be achievable at a facility with expertise and access to FDG PET imaging. There are no similar data upon which to draw an estimate for CMR. Considering the Schinkel *et al*. publication [38], which noted sensitivity of CMR to be between PET and standard care modalities and based on expert consensus from our IMAGE-HF workshop (16 December 2008 in Toronto, Canada), we estimate the event rate for CMR directed care would lie between the above values at 34%. Hence, an overall rate for the alternative (PET, CMR) modalities would be approximately 30%. The rates are considered conservative since the mean duration of follow-up will be 2 years, whereas the PARR-2 study was 1 year.

For the primary hypothesis, using the two-sided log-rank test for comparing advanced (PET + CMR) versus standard modalities with a 2:1 patient allocation, a sample size of 495 patients (of which 330 are allocated to the advance modality and 165 are allocated to the standard modality) would be needed in order to detect a difference after 1 year in the composite clinical endpoint of 30% for the advanced modalities (PET, CMR) compared to 40% for standard care modalities (SPECT). This is calculated with a level of significance of 0.05 and power of 80%, and assuming a uniform accrual of patients over the 2.5 year recruitment period, a 1 year minimum follow-up period and a 10% loss from each study group. The difference of 10% was considered to be a minimal clinically important difference based on a consensus of the IMAGE-HF investigators.

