#### Analysis populations

For the purposes of data analysis, three study populations will be considered: Intent-to-treat (ITT) Population, As-Treated Population and Per-protocol Population. The ITT population will be used for the main analysis for all primary and secondary objectives, except for the safety analysis where the as-treated population will be used. As a secondary analysis, the analyses will be repeated for the as-treated and per-protocol populations.

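### The Registry section implies that advanced-imaging registry patients are in the primary comparison, the Sample size section implies that they are not, and no other section settles it

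*Protocol article*

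**What the plan says.** Four sections of the protocol article bear on who is in the primary analysis.

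- **Registry.** "The registry patients for advanced imaging will be considered in the sample size calculation and data analysis (see below"). The sentence continues with a contrast: "the small number of patients expected to be part of the SPECT registry will not be considered in the primary analysis".
- **Sample size.** The primary hypothesis is sized "using the two-sided log-rank test for comparing advanced (PET + CMR) versus standard modalities with a 2:1 patient allocation", giving 495 patients (330 advanced, 165 standard). The 766 advanced registry patients (383 PET, 383 CMR) come in under the secondary hypothesis, PET versus CMR, where they join the 330 randomised to make 1,096. The total is 1,096 + 165 = 1,261.
- **Analysis populations.** "The ITT population will be used for the main analysis for all primary and secondary objectives", with safety as the exception. The article does not say whether this population is confined to randomised patients.
- **Primary analysis (advanced versus standard imaging).** Advanced is compared with SPECT by Kaplan-Meier curves and the log-rank test, with no mention of randomised patients. Then: "Potential confounding variables of the relationship between the imaging technologies and the primary endpoint will be assessed", with propensity scores if needed and a Cox model adjusted for baseline differences. Time to imaging and time to therapy are among the factors listed for the propensity score.

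**The concern.** The contrast in the Registry section makes sense only if the two registries are treated differently in the primary analysis. If both were excluded, there would be no reason to single out SPECT. If the sentence concerned PET versus CMR, excluding SPECT patients would be empty, because they have no place in that comparison. Read by itself, then, the section puts the advanced registry into the primary comparison and leaves the SPECT registry out.

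The other sections do not repair this. The ITT label is applied to every objective, including PET versus CMR, which needs 766 patients who were never randomised; so ITT as used here cannot simply mean randomised patients. The confounding and propensity-score text for the primary analysis is nearly the same as that for PET versus CMR, which does contain registry patients.

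What is at stake is the randomised basis of the primary result. If the advanced registry is pooled in, clinical selection acts on one arm only. The protocol expects confounding by indication among registry patients, but its allowance (R = 0.25) is made only for PET versus CMR. The trial is also open label, so a primary set that can be read in two ways leaves room to choose between them once outcomes are known.

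**Working it through.** **1. Does the primary sample size need the registry?**

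Inputs, all from the Sample size section: "30% for the advanced modalities (PET, CMR) compared to 40% for standard care modalities (SPECT") at one year; two-sided alpha 0.05; power 80%; 2:1 allocation; 2.5 years' uniform accrual; 1 year minimum follow-up; 10% loss.

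- Exponential hazards: advanced -ln(0.7) = 0.357, standard -ln(0.6) = 0.511 per year; hazard ratio 0.698.
- Event probability: 1 - [exp(-λ) - exp(-3.5λ)]/(2.5λ), giving 0.537 advanced, 0.661 standard and (2 × 0.537 + 0.661)/3 = 0.578 overall.
- Lachin-Foulkes type formula with v(λ) = λ²/P(event) and pooled hazard 0.408: N = [1.96√(4.5 v(0.408)) + 0.842√(1.5 v(0.357) + 3 v(0.511))]² / (0.357 - 0.511)² = 449. Dividing by 0.9 gives 499; modelling loss as 10% per year gives 496.
- Other formulas bracket the figure: Schoenfeld, 274 events, 526 patients after loss; Freedman, 248 events, 476 patients after loss.

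The plan's 495 is therefore reproduced from randomised patients alone.

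**2. Where does the registry enter the sizing?**

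PET versus CMR: (1.96 + 0.842)² / (0.25 × [ln 1.4]²) = 277.3 events. Then 277.3 / [0.30 × (1 - 0.25²)] / 0.9 = 1,096, an exact match. The 766 registry patients are needed here and only here.

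**3. The two readings side by side**

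| | Registry section, taken literally | Sample size section |
|---|---|---|
| Advanced arm | 330 + 766 = 1,096 | 330 |
| Standard arm | 165 | 165 |
| Ratio | 6.64:1 | 2:1 |
| Advanced arm not randomised | 766/1,096 = 70% | 0% |

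Pooling would look attractive: with 10% loss and the planned effect there would be about 628 events and nominal Schoenfeld power of about 86%, against about 258 events and 78% for the 495 by the same formula. That gain assumes registry patients carry the same underlying risk as randomised ones.

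**4. Size of the problem under the literal reading**

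Assume no true imaging effect, a hazard of 0.511 per year in all randomised patients, c times that in the registry, 10% loss and no covariate adjustment. The documents give no value for c, so a range is shown. Worked case, c = 0.8:

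- Registry event probability 0.584.
- Advanced events: 0.9 × (330 × 0.661 + 766 × 0.584) = 599, over 1,369 person-years, so the hazard is 0.437.
- Standard events: 0.9 × 165 × 0.661 = 98.
- Apparent hazard ratio 0.437/0.511 = 0.856; ln = -0.155; standard error √(1/599 + 1/98) = 0.109; expected z = -1.43.
- Chance of |z| > 1.96: about 30%.

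| Registry hazard relative to randomised | Apparent HR | Type I error, approximation | Type I error, simulated log-rank |
|---|---|---|---|
| 0.9 | 0.93 | 10% | 11-12% |
| 0.8 | 0.86 | 30% | 30-34% |
| 0.7 | 0.78 | 62% | 62-66% |

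The simulated ranges cover runs without loss and with 10% loss per year. Nearly all false rejections favour advanced imaging. A higher-risk registry works the other way: at 1.25 times the hazard the apparent ratio is 1.17, with about 30% rejection against advanced imaging.

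**The case against.** The strongest reply is that the Registry section refers the reader onward, and what follows is explicit: 495 patients at 2:1 for the primary hypothesis, and the registry introduced only under the secondary one, with its own confounding allowance. A planned 6.64:1 comparison would hardly be described as 2:1. The article also condenses a fuller protocol, which may define ITT. Propensity scores are conditional on need, and the near-identical text under PET versus CMR may be reused wording.

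Most of this stands, and it limits what may be concluded. A reader might infer that the sponsor plans to pool, or that the primary result has already lost its randomised basis. The documents do not support that: pooling is permitted, not required, and the sizing argues against it. A reader might also infer that the planned test has the error rates above. They hold only under the literal reading, with assumed registry hazards and no adjustment; the adjusted Cox model was not evaluated.

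Two further inferences fail. The abstract's statement that "AIMI-HF will be the largest randomized trial evaluating the role of standard and advanced imaging modalities" cannot be tested, because the documents do not give the sizes of the other trials; 495 could still be the largest. And the mention of propensity scores is not an error in itself: adjustment for baseline covariates is legitimate in a randomised comparison.

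What the reply does not remove is the contrast in the Registry section. That is stated text, not an omission, and it conflicts with the sizing. A fuller document that restricts the primary set to randomised patients would still be contradicted by it.

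**Conclusion.** The point holds as an internal contradiction about the composition of the primary analysis set. One section implies 1,096 v 165, another 330 v 165, and neither the ITT statement nor the primary analysis section decides between them. No sample-size figure is wrong.

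The harm is conditional. If the Registry section is followed literally, modest differences in registry risk are enough to matter: type I error of about 10-12% at a 10% lower hazard, 30-34% at 20% and 62-66% at 30%. This rests on exponential survival, the protocol's accrual and follow-up, an unadjusted test and assumed registry hazards. It needs correcting before analysis because it decides who is in the primary comparison of an open-label trial.

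**What to change.** 1. In the Registry, Analysis populations and Primary analysis sections, state that the primary log-rank and Cox analyses include all patients randomised to advanced or standard imaging (planned 495), analysed as randomised, and that no registry patient of either kind enters them. Adding the SPECT registry for symmetry would not restore randomisation.
2. Limit adjustment in that comparison to covariates fixed before randomisation. Time to imaging and time to therapy, which arise after allocation, should not be used there. Propensity scores as such need not be banned.
3. Use the advanced registry only for PET versus CMR and for analyses labelled observational, and define the PET versus CMR set separately from ITT.
4. In the abstract and wherever size is reported, give 495 randomised plus 766 registry patients instead of 1,261 alone.

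The cost is wording in the protocol and the SAP. The primary sample size was computed on 495 randomised patients and PET versus CMR keeps its 1,096, so no planned patients or planned power are lost.
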